### Statistical analyses

Data will be analyzed using the Statistical Package for the Social Sciences (SPSS), version 24.0 or higher (SPSS, Chicago, IL, USA), and reported following the Consolidated Standards of Reporting Trials (CONSORT) guidelines. Normality of continuous data will be tested with the Shapiro-Wilk test. Homogeneity of variances will be tested using Levene’s test. The analysis will be performed on an intention to treat basis. A two-sided *p* value < 0.05 will be taken as threshold of statistical significance in all statistical tests. Procedures will be implemented to reduce missing data. In previous studies of the principal investigator’s department, these procedures led to < 5% missing data [54]. If necessary, missing values will be replaced using multiple imputation following the predictive mean matching method, using ten imputations.

Descriptive analysis will be performed in order to report the outcome measures for both treatment arms. For categorical data, numbers and frequencies will be reported. For continuous data, the mean and SD (parametric data) or the mean and percentiles (non-parametric data) will be reported.

Next, univariate analysis will be performed in order to test for statistical significance of differences between the primary and secondary outcome measures across the two groups. A chi-squared analysis or Fisher’s exact test will be used for statistical testing of categorical data (e.g., the primary outcome, pneumonia). Continuous data (i.e., hospital length of stay) will be tested using Student’s *t* test (parametric data; with equal variance or unequal variance whichever applies according to Levene’s test) or Mann-Whitney *U* test (non-parametric data).

Multivariable analysis will be done as secondary analysis. A logistic regression model will be developed, with pneumonia as dependent variable and treatment as covariate. Nonoperative treatment will serve as reference category. Baseline and injury-related variables that may potentially confound the association between treatment and outcome will be included in this model as covariate. These will be selected from literature and from data of this study (see Other data collected). Known potential confounders according to literature data are the number of rib fractures and age. Other potential confounders collected as part of this study are gender, ASA, COPD, osteoporosis, and additional injuries (ISS ≥ 16 versus ISS < 16, and presence versus absence of severe injuries (AIS ≥ 3) for any body region). Variables that produce a *p* value < 0.2 in the univariate analysis will be included in the regression model. Odds ratios will be reported with their 95% confidence interval and *p* value.

Continuous outcomes repeatedly measured over time will be compared between treatment groups using linear mixed-effects regression models (with fixed effects for treatment and other covariates like gender and age, if applicable). The interaction between treatment and time will be included to test for differences between groups over time. For each follow-up moment, the estimated marginal mean will be computed per treatment group and compared post hoc with a Bonferroni test in order to correct for multiple testing.

Other continuous and binomial variables will be tested with multivariable linear and binary logistic regression models, respectively. The outcome measure will be entered as dependent variable and treatment as covariate. Nonoperative treatment will serve as the reference group. Baseline and injury-related variables that may potentially confound the association between treatment and outcome will be included in the models as covariate. Coefficients will be reported with their 95% confidence interval and *p* value.

Economic evaluation will be done from a societal perspective with iMCQ and iPCQ questionnaires. Health care costs and lost productivity until 1 year after trauma will be measured. Cost prices of the standardized referral strategy will be determined by a bottom-up micro-costing method. The incremental cost-effectiveness ratio of ORIF versus nonoperative treatment will be expressed as costs per pneumonia prevented, with confidence ellipses and acceptability curves. A cost-utility analysis, with QALY (based on the EQ-5D summary score) as outcome measure, will also be done.

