### Recruitment and randomization

Eligible persons presenting to the emergency department (ED) or referred from another hospital, with multiple, simple rib fractures will be informed about the trial at the ED or at the surgical ward after admission. After explanation of the study, eligible patients will receive written information and a consent form from the attending physician, the clinical investigator, or a research assistant. Patients meeting all eligibility criteria will be recruited within 1 day after hospital admission. As surgical rib fixation appears to be most beneficial when performed within 72 h after trauma, patients are stimulated to decide within this period. However, informed consent can be given by the patient as long as rib fixation can be carried out within 1 week after trauma. Should patients not be able to sign informed consent themselves, a legal representative will receive oral and written information about the study, in the hospital, by the attending physician, the clinical investigator, or a research assistant, and will be asked to consent with participation of the patient.

After signing informed consent by patient or proxy, participants are allocated to one of the two study arms (surgical stabilization or nonoperative treatment) using a web-based randomization program that will be available 24 h a day. Allocation will be at random and concealed, in a 1:1 ratio, and will be stratified by site. Variable block sizes will be used; in each block, both treatments will be represented equally. As the intervention cannot be blinded, it will in no case be necessary to break the randomization code.

As with many surgical trials, patients and surgeons cannot be blinded for the intervention. In order to reduce bias as much as possible, a research physician or research assistant will perform the follow-up measurements using a standardized protocol. Also, the treating surgeon or ICU doctor will identify the primary outcome (i.e., pneumonia) based on the definition as mentioned under outcome measures.

Participation is on a voluntary basis and participants are allowed to withdraw from the study at any time without specifying why. The general practitioner will be informed about the patients’ participation.

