### Sample size calculation

Calculation of the required sample size for the primary analysis is based on data from a Cochrane review and a large retrospective analysis [7, 32]. These studies suggest a pneumonia rate of 35% in nonoperatively treated patients and 15% in operatively treated patients with multiple rib fractures. This difference is considered clinically relevant. A two-sided test with an α level of 0.05 and a β level of 0.2 requires 72 patients in each group. In order to account for 25% loss of patients to follow-up and mortality, a sample size of 90 patients per group is needed. In total, 180 patients will be included and randomized.

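### The number of imputations is fixed at ten whatever fraction is missing; results remain valid, but if missingness were high a pooled p value near 0.05 would depend noticeably on the random seed

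*Protocol article*

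**What the plan says.** All references are to the protocol article.

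- **Statistical analyses**, on missing data: "If necessary, missing values will be replaced using multiple imputation following the predictive mean matching method, using ten imputations". The number is a constant, not tied to the amount missing.
- The sentence just before it reports past experience: "In previous studies of the principal investigator’s department, these procedures led to < 5% missing data".
- The same section applies one threshold throughout: a two-sided p "value < 0.05 will be taken as threshold of statistical significance in all statistical tests".
- **Sample size calculation**: "These studies suggest a pneumonia rate of 35% in nonoperatively treated patients and 15% in operatively treated patients with multiple rib fractures". Then: "A two-sided test with an α level of 0.05 and a β level of 0.2 requires 72 patients in each group". The inflation step reads: "In order to account for 25% loss of patients to follow-up and mortality, a sample size of 90 patients per group is needed".
- **Primary outcome measure** is pneumonia within 30 days. **Study procedures** follow patients to 12 months. Repeatedly measured continuous outcomes are analysed with linear mixed-effects models; costs and QALYs come from the economic evaluation.

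**The concern.** Multiple imputation draws random values, so the pooled estimate, its standard error and its p value change from one seed to another. The change shrinks as the number of imputations grows and increases with the fraction of missing information. The article mentions two very different levels of loss: under 5% in earlier studies, and a 25% allowance in the sample size. Imputation is conditional on need, so it matters most when the lower level is not met, yet the number of imputations is the same in both cases. With a hard threshold at 0.05, a borderline result could be declared significant by one analyst and not by another who follows the same plan on the same data.

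**Working it through.** **Inputs from the article.** m = 10 imputations; 35% v 15%; two-sided α 0.05; power 0.80; 72 per group inflated to 90; loss allowance 25%; under 5% missing in earlier studies.

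**Assumptions.** The fraction of missing information (FMI) equals the fraction missing, which is an upper case because useful predictors would lower it. Values are missing completely at random. The pooled quantity is a risk difference.

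**1. The plan's own figure.** The article derives nothing for the ten imputations, so the only figure to reproduce is the sample size:

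n = [1.96·√(2·0.25·0.75) + 0.842·√(0.35·0.65 + 0.15·0.85)]² / 0.20² = 72.4,

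which is 73 rounded up, against 72 stated. Then 72 × 1.25 = 90. A group of 90 falls back to 72 after losing 18/90 = 20%, so the relevant upper range of loss is 20-25%.

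**2. Seed noise by formula.** In units of the standard error, the noise of the pooled estimate is √(FMI/m). Relative efficiency is 1/(1 + FMI/m). The last column is the 95% seed range of p for a result centred on z = 1.96, that is z = 1.96 ± 1.96·√(FMI/m).

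| FMI | Noise, m = 10 | Relative efficiency | Seed range of p |
|---|---|---|---|
| 0.25 | √0.025 = 0.158 | 97.6% | 0.023-0.099 |
| 0.20 | √0.020 = 0.141 | 98.0% | 0.025-0.092 |
| 0.05 | √0.005 = 0.071 | 99.5% | 0.036-0.069 |

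At FMI 0.25 and m = 100 the noise is √0.0025 = 0.050.

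**3. How often two seeds disagree on p < 0.05.** Simulated trials with 90 per arm, 35% v 15%, within-arm imputation from a Beta posterior, Rubin's rules with small-sample degrees of freedom, and two independent seeds per data set. Ranges are across separate simulation runs.

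| Missing | m = 10 | m = 50 | m = 100 |
|---|---|---|---|
| 25% | 6.1-7.4% | 2.6-2.9% | 1.9-2.2% |
| 20% | 5.6% | not run | 1.7% |
| 5% | 1.5-2.2% (most runs 1.5-1.7%) | 0.8% | 0.5-0.6% |

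Disagreement is more common when power is lower: for 35% v 20% with 25% missing it is 9.0% at m = 10 and 2.9% at m = 100.

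**4. Given data sets near the threshold.** The observed data are held fixed and only the seed varies, with 20,000 seeds per setting. The large-m p is the value approached as the number of imputations grows.

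| Missing | Large-m p | Seeds with p < 0.05: m = 10 | m = 50 | m = 100 |
|---|---|---|---|---|
| 25% | 0.033 | 75% | 97% | 99.7% |
| 25% | 0.056 | 36% | 29% | 22% |
| 5% | 0.040 | 88% | 99.7% | 100% |

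In the first row the 95% seed range of p is 0.013-0.088 at m = 10 and 0.025-0.045 at m = 100.

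**5. Validity.** With 25% missing and no true difference (25% in both arms), the rejection rate at m = 10 is 4.9%. Power for 35% v 15% with 25% missing is 77% at m = 10 and 79% at m = 100.

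**The case against.** The strongest reply is that the 25% is not an imputation rate. It is a sample-size allowance for loss and mortality together, in a trial with 12 months of follow-up, and patients who die may have known pneumonia status. The imputation sentence is conditional and follows a report of under 5% missing. The primary outcome is read at 30 days, with daily evaluation in hospital, visits at 2 weeks and 1 month, checks against the medical records and a monitor's review of the files. A reader might infer that the plan expects to impute a quarter of the pneumonia outcomes and that the primary verdict would turn on the seed. The documents do not support that. This part of the reply stands in full.

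Three further replies also stand:

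- Ten imputations give valid inference, with close to full efficiency.
- Mixed models use all available observations, which covers the repeatedly measured continuous outcomes.
- Seed dependence very close to 0.05 exists at any finite number of imputations, as the 22% at m = 100 shows.

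The simulations are also simpler than the plan. They use no covariates, do not use predictive mean matching, and pool a risk difference where the article plans a chi-squared or Fisher's exact test. The baseline and injury variables that the article lists could lower the missing information. The figures are therefore an upper case.

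A rule linking the number of imputations to observed missingness, or a stated seed, may properly sit in an analysis plan that is not shown, so its absence is no fault. What the reply does not answer is that the article does state a number, and that number is less reproducible than a larger one available at no real cost.

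**Conclusion.** The point holds as a small, free improvement in reproducibility. With missingness at the 20-25% that the sample size allows for, ten imputations leave seed noise of 0.14-0.16 standard errors and about 6-7% disagreement between seeds, against about 1.5-2% at 100. At under 5% missing the contrast is about 1.5% against 0.5%. All of these rest on the FMI assumption and on 35% v 15% with 90 per arm.

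The exposure lies mainly in 12-month outcomes outside the mixed models: cumulative costs, QALYs and binary outcomes such as secondary interventions. It is less likely to touch 30-day pneumonia. A reader might also take this to mean that analyses with ten imputations are biased or have the wrong error rate; the 4.9% rejection rate and 97.6% efficiency at 25% missing show otherwise. The loss is about two points of power and some repeatability near the threshold.

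**What to change.** In the imputation sentence under Statistical analyses, change the number from ten to 100, or at least 50, and record the random seed before the analysis is run. Reporting the Monte Carlo error of pooled estimates would show the reader how much seed noise remains. This narrows seed dependence near 0.05 but does not abolish it. The cost is computing time only: no change to the sample size, the data collected or the other analyses.

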## Methods/design

### Objective

The primary aim of this trial is to investigate the effect of ORIF versus nonoperative treatment on the occurrence of pneumonia within 30 days after trauma in adult patients who sustained multiple simple fractured ribs. The secondary aims are to investigate the effect of treatment on the need for and duration of mechanical ventilation, level of thoracic pain and analgesics use, (recovery of) pulmonary function, hospital and ICU length of stay, thoracic injury-related and surgery-related complications and mortality, secondary interventions, quality of life, and total costs (in-hospital and socio-economic) of treatment, health care consumption, and work absence. At the end, a cost-effectiveness analysis will be done.

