#### Secondary outcome measures

The secondary outcome measures are:Need and duration of mechanical ventilation in days. The number of days of invasive mechanical ventilation (by endotracheal tube or tracheostomy) from intubation until successful weaning will be determined. The need for mechanical ventilation will be evaluated based on arterial blood gas analysis and clinical performance of the patient. The duration of mechanical ventilation will be calculated from the dates of intubation and extubation. Re-intubation within 30 days will be recorded as well.Level of thoracic pain (NRS) and analgesics use. Thoracic pain will be determined using an 11-point Numeric Rating Scale (NRS) in which 0 implicates no pain and 10 the worst possible pain. Five thoracic pain levels will be analyzed: pain in rest, at night, during daily activities (e.g., work or hobbies), during maximal inspiration, and during self-care. Analgesics use during admission will be extracted from the medical files. After discharge, analgesics use will be asked for during the follow-up visits. Daily narcotic requirement will be calculated using an equivalence scale for 30 mg/day oral morphine.(Recovery of) pulmonary function. The parameters tidal volume (TV), forced vital capacity (FVC), inspiratory capacity (IC_lung_), and forced expiratory volume at 1 second (FEV_1_) will be determined using spirometry. Spirometry will be done by a member of the research team. During the spirometry, the patient has to inhale actively and exhale with maximum force possible. The mean of three tests will be calculated.Hospital length of stay expressed in days. This will be calculated as the time between admission and discharge from the hospital. Re-admission within 30 days will be added. Re-admission for thoracic reasons after 30 days and up to 12 months will be counted separately.ICU length of stay expressed in days. This will be calculated similarly to the hospital length of stay.Thoracic injury-related complications and mortality. The occurrence of thoracic injury-related complications will be recorded from the medical charts during clinical admission and each follow-up visit. Complications will be categorized for level of severity and treatment necessity according to the Clavien-Dindo classification [43]. Complications will include empyema (as diagnosed on CT scan, in presence of fever or positive cultures in the drained fluid), (retained) hydrothorax (a heterogeneous fluid collection with Hounsfield unit readings of 35–70 and evidence of pleural thickening) [44], nonunion (diagnosed on CT scan or operatively, at least 6 months after trauma) [45], and other (all other complications as judged by the treating physician). If mortality is caused by the thoracic injury or complication of thoracic injury, it will be counted in rates of mortality. Death caused by other reasons will be noted but excluded in this calculation.Surgery-related complications. The ORIF group can also develop hardware-related complications or failure. Hardware-related complication is superficial and deep wound infection which is defined as redness, tenderness, and warmth surrounding and in direct contact with the postoperative wound. Superficial infection leads to oral or IV antibiotics, and deep infection leads to surgical activity such as stitch removal of exploration of the wound. Hardware failure is defined as loosening of the plate, secondary dislocation of fixation material, malposition of hardware, and broken plates or splints.Secondary interventions to resolve complications. Secondary interventions within 12 months after trauma to relieve pain, treat infection, or other rib fracture-related problems will include the following: antibiotic therapy (both oral and intravenous), additional surgical interventions (e.g., surgical stabilization of nonunion, evacuation of hematoma, evacuation of empyema, removal of failed hardware, symptomatic hardware removal, and treatment of infection), and additional percutaneous interventions (e.g., for persistent bleeding intercostal artery, intraparenchymal bleeding, drainage of infection, and drainage of pleural fluid).Health-related quality of life measured using the Short Form-12 (SF-12) and EuroQoL-5D (EQ-5D) questionnaires. The SF-12 analyzes global health status, functional scale, and symptom scale. The score will be calculated based on eight domains and summarized into a Physical Component Summary (PCS) and Mental Component Summary (MCS). Data will be reported as utility score, ranging from 0 to 1 with a higher value indicating better quality of life. As a reference, the US population of 1998 will be used [46]. The EQ-5D is the most commonly used quality of life instrument for (rib) fracture patients [47, 48]. The EQ-5D is recommended for assessment of quality of life in trauma patients, especially for economic evaluation [49, 50]. The EQ-5D-5 L descriptive system consists of five dimensions of health (mobility, self-care, usual activities, pain/discomfort, and anxiety/depression), each with five possible answers. The patients’ health states will be converted into a utility score using the Dutch tariff [51]. Utility scores range from 0 to 1 with lower scores indicating poorer quality of life.Cost-effectiveness and health care consumption. Economic evaluations will be done from a societal perspective. The validated Medical Consumption Questionnaire (iMCQ) and Production Consumption Questionnaire (iPCQ) will be used. iMCQ details medical specialist care, physical therapy, hospitalization, nursing home, home care, and other costs directly associated with diagnosis, treatment, and rehabilitation. iPCQ comprises work resumption and production losses. Health care costs and lost productivity until 1 year after trauma will be measured in accordance with economic guidelines [52].

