## Discussion

The FixCon trial studies outcome after operative versus nonoperative treatment of multiple simple rib fractures. With high rates of morbidity and low quality of life at long-term follow-up, multiple simple rib fractures cause a serious health hazard. With favorable results in flail chest patients, operative treatment might also result in better clinical and functional recovery of patients with multiple simple rib fractures. Improved outcome could translate into less pulmonary complications, shorter hospital stay, less pain, improved quality of life, and quicker return to normal activities or work compared with nonoperative treatment. Operative treatment, while initially yielding higher economic costs, could then result in less financial needs, due to less health care use and less productivity loss. As a result, primarily performing surgery could be both improving patient outcome and being the most cost-effective treatment modality.

To the best of our knowledge, this is the first multicenter randomized controlled trial to evaluate outcome from patient, medical, and economic perspectives in patients suffering from multiple simple rib fractures. Twelve hospitals in the Netherlands will participate in this trial.

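### As written, the normality rule sends one-year costs to a Mann-Whitney test, whose p value can disagree with the difference in mean cost that the economic evaluation uses

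*Protocol article*

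**What the plan says.** All references are to the protocol article.

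- **Scope of the test rule (Statistical analyses).** Univariate analysis is done to "test for statistical significance of differences between the primary and secondary outcome measures across the two groups". The section does not set any secondary outcome apart.
- **Choice of test (same section).** "Normality of continuous data will be tested with the Shapiro-Wilk test". Continuous data then get a Student's t "test (parametric data; with equal variance or unequal variance whichever applies according to Levene’s test) or Mann-Whitney" U test, the latter when the data are judged non-parametric. A two-sided p "value < 0.05 will be taken as threshold of statistical significance in all statistical tests".
- **Costs are a secondary outcome.** The Objective section lists among the secondary aims the effect of treatment on "total costs (in-hospital and socio-economic) of treatment, health care consumption, and work absence". The last item under Secondary outcome measures says: "Health care costs and lost productivity until 1 year after trauma will be measured in accordance with economic guidelines".
- **Economic paragraph (end of Statistical analyses).** It plans an ICER per pneumonia avoided, with ellipses and acceptability curves, and a cost-utility analysis. It names no test for costs and does not say that it replaces the univariate test.
- **Expected cost pattern (Discussion).** "Operative treatment, while initially yielding higher economic costs, could then result in less financial needs".

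**The concern.** The cost question concerns means: an arm's total cost is its mean times its number of patients, and the ICER numerator is a difference in means. Mann-Whitney asks something else, namely whether a random ORIF patient is more likely than not to cost more than a random control.

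The two questions agree when both arms have the same distributional shape. They can part when one arm carries an extra cost in nearly every patient and gains it back through fewer or cheaper expensive courses. The Discussion hopes for that pattern, and the assumed fall in pneumonia suggests that much of the saving would fall on a minority.

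At stake is the p value printed beside total costs. It could be significant when mean costs are equal, or label ORIF as dearer when ORIF saves money on average, in the same report as an incremental cost of the opposite sign.

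**Working it through.** **1. Does the rule reach costs?** Read literally, yes. The univariate rule covers the secondary outcome measures, costs are among them, and no exemption is stated. The documents give no cost distribution, but one-year costs are bounded at zero with a long right tail. In simulated lognormal costs at 72 or 90 per arm, Shapiro-Wilk rejected in 100% of runs, so such costs go to Mann-Whitney.

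**2. Inputs.** From Sample size calculation: 72 per group needed, 90 randomized (72 × 1.25), pneumonia 35% nonoperative and 15% operative. From Statistical analyses: two-sided 0.05. The plan states no cost figure or error rate to reproduce. *All cost values below are assumptions*, in arbitrary units, with 4,000 simulated trials per setting. Welch is the unequal-variance t test.

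**3. Model A: fixed surgery cost f, savings proportional across patients.** Control cost = 15,000·exp(Z) and ORIF cost = f + (15,000 − f)·exp(Z), with Z normal, mean −s²/2 and SD s. Since E[exp(Z)] = 1, both means are 15,000. The medians differ by f·(1 − exp(−s²/2)). For s = 1 and f = 5,000 that is 5,000 × 0.393 = about 1,970, with ORIF higher although the means are equal.

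| f | log-SD s | Mann-Whitney, 72 per arm | Mann-Whitney, 90 per arm | Welch |
|---|---|---|---|---|
| 0 (same shape) | 0.8-1.2 | about 5% | about 5% | 4-6% |
| 2,000 | 0.8 | 9-10% | 11% | 4-6% |
| 2,000 | 1.0 | 13-14% | 17% | 4-6% |
| 3,000 | 0.8-1.2 | 16-42% | 18-50% | 4-6% |
| 5,000 | 0.8-1.2 | 33-75% | 42-83% | 4-6% |

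For f above 0, nearly all rejections point to ORIF as dearer.

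**4. Model B: savings only through pneumonia.** Base cost is lognormal with mean 10,000 and log-SD 0.8-1.2. A pneumonia cost X falls on 35% v 15% of patients, and each ORIF patient has a surcharge d. Equal means need d = (0.35 − 0.15)·X = 0.2X. Check with X = 10,000 and d = 2,000: control 10,000 + 0.35 × 10,000 = 13,500; ORIF 10,000 + 2,000 + 0.15 × 10,000 = 13,500.

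| d | X = d/0.2 | Mann-Whitney, 72-90 per arm | Welch |
|---|---|---|---|
| 2,000 | 10,000 | 5-8% | 4-6% |
| 3,000 | 15,000 | 8-13% | 4-6% |
| 5,000 | 25,000 | 21-32% | 4-6% |

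**5. When ORIF truly saves.** Model A with ORIF mean 13,000 against 15,000, s = 1 and 90 per arm. Mann-Whitney is significant for ORIF as dearer in about 2-3% (f = 2,000), 8% (f = 3,000) and 29-31% (f = 5,000) of trials. It is significant for ORIF as cheaper in under 1% at f = 3,000 and f = 5,000. At f = 2,000 the wrong-direction rate is no more than the 2.5% expected in one tail by chance.

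**The case against.** **The economic paragraph may be meant to govern costs.** The article's example of a continuous outcome is hospital length of stay, and costs have their own paragraph with their own methods. A specific provision is naturally read as overriding a general one. This is a fair account of what may be intended, but the text does not say it. The general rule names the secondary outcomes without exception, and the economic paragraph gives no alternative comparison of costs. This is therefore a stated rule that misdirects a test, and not merely detail left to a fuller document.

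**Mean-based analyses are already planned.** This stands, and it limits the harm. The ICER, its ellipses and the acceptability curves rest on mean costs. The multivariable linear regression for other continuous outcomes gives a mean difference with a 95% interval, although multivariable analysis is introduced as secondary. Non-parametric data are to be described by the mean with percentiles, so arm means would be reported. A reader might infer that the cost-effectiveness conclusion itself rests on a rank test. The documents do not support that.

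**The size depends on assumptions.** This also stands. Proportional savings (Model A) do not represent savings confined to fewer patients. Model B is closer to that mechanism, and its rates are markedly lower and near nominal at a surcharge of 2,000.

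**Conclusion.** The point holds in limited form. As written, the plan yields a first-line cost p value from a test that does not address mean cost, in the setting where the two are likely to diverge. Under the stated assumptions, Mann-Whitney rejects at equal means in about 10-83% of trials (proportional savings) or about 5-32% (savings through pneumonia only), against about 4-6% for Welch.

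These ranges describe the assumed costs, not this trial. There is no excess when both arms have the same shape. More extreme assumptions go higher: a variant of Model B with a pneumonia cost of 40,000, a surcharge of 8,000 and log-SD 0.5-1.0 gave 56-88%. A reader might also infer that the surgery bill all but guarantees a significant result against ORIF. That is not supported: when ORIF saves 2,000 on average, this occurs in about 2-3% to 31% of the settings tried.

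The consequence is a possible conflict between one p value and the incremental cost in the same report. It is worth correcting because costs are a stated secondary aim and the correction is simple.

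**What to change.** In Statistical analyses, at the univariate tests and again in the economic paragraph, state:

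*Costs (total, health care and productivity) are exempt from the normality rule. They are compared as the difference in arithmetic means, the numerator of the cost-effectiveness ratio, with a bootstrap or unequal-variance 95% confidence interval. No rank test is used for costs.*

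This changes wording only and needs no new data. The price is that the interval for skewed costs will be wide, so the result may look less decisive than a rank test would suggest.
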